### Potential confounders

***Demographic and disease factors*** will be collected including years in oncology practice and years in current position (staff only); age, gender, marital status, education, postcode, ATSI status (staff and patients); and cancer type and stage of disease (patients only).

**Additional secondary outcomes** include the prevalence of anxiety and depression over time, accessed from the ADAPT Portal.

### Safety reporting

All adverse events (AEs) and serious adverse events (SAEs) related to implementing the ADAPT CP will be recorded concisely using standard terms.

The interventions being evaluated in this study are targeted at cancer service staff. It is not envisaged that cancer service staff will experience any adverse events. In the unlikely occurrence that attendance at a training or information session, completion of a survey or an interview does result in an adverse event, the relevant ethics committee will be notified. As screening and management of anxiety and depression will be introduced as standard practice, the reporting of adverse events related to anxiety and depression will not be reported as a study related AE event. There are no safety endpoints and no criteria for early study termination.

### Data management

All data will be stored in locked filing cabinets in a locked office at The University of Sydney or scanned and stored in password protected files and kept at the University of Sydney on a secure server. Electronic data will be password protected and kept at The University of Sydney on a secure server, which is backed up daily. Study-related records for all participants will be retained in a secure storage facility for at least 7 years after the completion of the research, according to the National Health and Medical Research Council requirements. These include: participant files, study protocol, signed consent forms, CRFs, questionnaires, ethics correspondence and approvals, other regulatory documentation, and other documents pertaining to the conduct of the study. All relevant documentation according to the Data Management Plan will be held by the lead investigator at each participating site for the duration of the study. This study will adhere to PoCoG’s quality assurance processes, including adherence to standard operating procedures and regularly reporting of study progress to the organisation.

### Statistical methods

#### Sample size and justification

##### Power for primary endpoints

Based on cancer registry data for NSW (2009) (https://www.cancerinstitute.org.au/data-research/data-held-by-cinsw/nsw-cancer-registry), approximately 37,525 patients in NSW will be diagnosed with cancer in NSW each year. Based on prior epidemiological studies, 42–45% and 35–37% of these will experience mild depression or mild anxiety, respectively [3, 36, 37] and 22–36% and 20–30% will experience moderate to severe depression and/or anxiety respectively.

Based on incidence and prevalence of cancer in NSW, a conservative estimate of 464 screening events per site (total sample of 5568 screening events in 12 sites), there is at least 80% power to detect a difference in adherence rates of 30% in the Core and 60% in the Enhanced arm using a two-tailed test with Type 1 error rate of 5%. The sample size has been adjusted for the variance inflation factor due to the clustered design and can accommodate an intraclass correlation coefficient (ICC) as high as 0.14 to achieve 80% power and 0.10 to achieve 90% power [38, 39]. Although estimates of the ICC are not available, we expect the ICC will be within this range. Based on the Cancer Institute figures, we do not envisage any difficulty in recruiting the required sample for this study. Note that the number of screening events and projected sample size and power may be revised based on screening at the first three services.

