### Primary analyses

The primary analysis will be conducted using a generalized estimating equations (GEE) approach to account for the correlation of outcomes within a cluster (site) using an exchangeable covariance structure and a bias correction factor to account for the small number of clusters [39]. The dependent variable will be clinical pathway adherence and the exposure variable will be the intervention status (core versus enhanced). The unit of analysis will be at the patient level to accommodate the weighting required by unequal cluster (site) sizes. Other independent variables will be added to the model if they are independently associated with adherence and/or their inclusion in the model changes the linear coefficient of the intervention effect by more than 20% in absolute value (i.e. effect modifiers).

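### The stated 80% and 90% power at ICC 0.14 and 0.10 makes no visible allowance for having only 12 sites; with one, power is about 72–75% and 85–87%

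*Protocol article*

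**What the plan says.** Under Power for primary endpoints, the protocol article plans on "a conservative estimate of 464 screening events per site (total sample of 5568 screening events in 12 sites"). The target is "a difference in adherence rates of 30% in the Core and 60% in the Enhanced arm", with the test run two-sided at the 5% level. The only allowance for clustering that it describes is this: "The sample size has been adjusted for the variance inflation factor due to the clustered design". It then says that the design "can accommodate an intraclass correlation coefficient (ICC) as high as 0.14 to achieve 80% power and 0.10 to achieve 90% power". On the evidence for those values it says: "Although estimates of the ICC are not available, we expect the ICC will be within this range". The paragraph closes by noting that "the number of screening events and projected sample size and power may be revised based on screening at the first three services".

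Under Primary analyses, the article plans a patient-level GEE with an exchangeable structure and "a bias correction factor to account for the small number of clusters".

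**The concern.** A variance inflation factor corrects the size of the variance for clustering. It does not correct for how poorly that variance is estimated from few sites. With six sites per arm, the between-site variance rests on about 10 degrees of freedom, and a test that holds 5% must use a wider critical value than 1.96. The analysis section acknowledges the small number of clusters, but the power paragraph describes no matching allowance.

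This matters because no ICC estimate exists. The two ICC ceilings are therefore the reader's only guide to how much between-site variation the trial can tolerate. If they are too high, the trial looks better protected than it is. The remedy that comes to mind first, more screening events, would not help.

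**Working it through.** **Inputs.** From Power for primary endpoints: adherence 30% v 60% (difference 0.30), m = 464 events per site, 12 sites, two-sided 5%, ICC 0.14 and 0.10. Assumed: six sites per arm, all of equal size. Equal allocation is implied by the design but not stated as a ratio. The article does not name its formula, so the method below is inferred from the match.

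**Step 1: reproduce the stated figures.** Design effect DE = 1 + (m − 1) × ICC; effective n per arm = 6 × 464 / DE = 2784 / DE. The n required per arm by the normal formula (pooled variance under the null) is [1.96 √(2 × 0.45 × 0.55) + z √(0.30 × 0.70 + 0.60 × 0.40)]² / 0.30², with z = 0.84 for 80% and 1.28 for 90%.

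| | ICC 0.14 | ICC 0.10 |
|---|---|---|
| DE | 1 + 463 × 0.14 = 65.82 | 1 + 463 × 0.10 = 47.3 |
| Effective n per arm | 2784 / 65.82 = 42.3 | 2784 / 47.3 = 58.9 |
| Required n per arm | 42.0 (80%) | 55.7 (90%) |
| Power, normal quantiles | 80.3% | 91.5% |

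Solving the same formula for the largest ICC gives 0.141 for 80% and 0.106 for 90%, which agrees with the printed 0.14 and 0.10. Other normal-theory versions (unpooled, arcsine, log-odds) give 78–83% and 90–93%.

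**Step 2: allow for 12 sites.** Keep the effect and the effective n, and replace the normal reference by t. The noncentrality is 0.30 / √(0.45 / effective n), where 0.45 = 0.21 + 0.24. This is 2.91 at ICC 0.14 and 3.43 at ICC 0.10. Degrees of freedom are 12 − 2 = 10, or 9 or 8 if the size stratum or a covariate uses some.

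| | ICC 0.14 | ICC 0.10 |
|---|---|---|
| t, 10 df | 74.6% | 87.0% |
| t, 9 df | 73.5% | 86.2% |
| t, 8 df | 72.2% | 85.1% |
| Simulated t-test on site proportions (beta-binomial) | 72.4% | 85.1% |
| Pooled variance, 8–10 df | 68–71% | 82–84% |

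The 72–75% and 85–87% are the unpooled results. The pooled version is lower, so the range does not exaggerate the loss.

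**Step 3: ICC ceilings.** With t on 10 df and unpooled variance, 80% power holds up to ICC 0.122 and 90% up to 0.090. With pooled variance the limits are 0.111 and 0.082. Hence about 0.11–0.12 and 0.08–0.09.

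**Step 4: effect of more events per site.** As m grows, effective n per arm tends to 6 / ICC.

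- ICC 0.14: the limit is 6 / 0.14 = 42.9, against 42.3 now. Doubling to 928 events moves power on 10 df from 74.6% to 74.9%; the limit is 75.1%.
- ICC 0.10: the limit is 6 / 0.10 = 60, against 58.9 now. Power rises from 87.0% to at most 87.6%.

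For contrast, 14 sites (seven per arm, 12 df, unpooled) give 82.2% and 92.5%.

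**The case against.** The strongest reply is that the printed numbers are right for the adjustment they name. Normal rather than t quantiles is an approximation, not a slip of arithmetic, and its use here is inferred. The two ICCs are ceilings of an assumed range and not the planning value. At a lower ICC the trial has ample power, and the move in the ceilings is small beside the ignorance about the ICC itself. All of this stands and limits the severity. It does not rescue the statement, which claims particular powers at particular ICCs with a 5% test.

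The choice of reference distribution for the GEE test is detail that an article may leave to the analysis plan. That also stands, and its absence is not part of this point.

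Two stronger readings are tempting, and the documents support neither.

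- *The primary test will run at about 8% type I error.* Referring an unbiased site-level statistic to ±1.96 does give about 8%. A bias correction that inflates the variance by about 1.2 gives about 6%, since 1.96 × √1.2 = 2.147 and P(|t| > 2.147) on 10 df is 5.7%. The article names neither the correction nor the reference distribution, so the most one can say is 6–8%, and only if a 1.96 cut-off were used.
- *The planned revision is wrong.* The sentence names sample size and power as well as screening events, does not exclude adding sites, and never says that three services will be used to estimate the ICC. What can be said is that event counts alone would barely change power.

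**Conclusion.** The concern holds as a should-fix. At the stated ICC ceilings, 12 sites deliver about 72–75% power where 80% is claimed and 85–87% where 90% is claimed: a shortfall of about 5–8 and 3–5 percentage points. This rests on six equal-sized sites per arm, a t reference on 8–10 degrees of freedom and unpooled variance; unequal sites would lower power somewhat further. If the true ICC is no more than about 0.11 (for 80%) or 0.08 (for 90%), the stated power is still reached on 10 degrees of freedom. The planned estimator is unaffected and no bias follows. The planned small-cluster correction helps to protect the type I error but does not restore the power.

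**What to change.** In Power for primary endpoints, do one of two things, using the same small-cluster reference as the primary analysis:

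- restate power as about 72–75% at ICC 0.14 and 85–87% at ICC 0.10; or
- keep 80% and 90% and lower the ICC ceilings to about 0.11–0.12 and 0.08–0.09.

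State the formula and the assumption of six sites per arm. Add one sentence to the note on revision: any reassessment of power will rest on the number of sites and on the ICC estimated without regard to arm, because event counts alone barely change it.

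The cost is a few sentences and a slightly less favourable figure. No design change follows if the sponsor accepts the lower power or the lower ceilings. Keeping 80% and 90% at the present ICCs would take more sites; 14 would suffice on the unpooled calculation in the working (pooled variance gives 78.5% and just under 90%).

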##### Power for secondary endpoints

Secondary outcomes will use data from either the ADAPT Portal, relating to patient activity through the ADAPT CP, MBS/PBS, staff surveys, staff interviews, or ADAPT research team observational records. Given the expected large sample size of 5568 patients, power should be adequate to test the patient activity related secondary outcomes. For secondary outcomes using staff reported data we anticipate a minimum of 10 staff per site, with 12 sites participating (120) in total.

### Primary analyses

The primary analysis will be conducted using a generalized estimating equations (GEE) approach to account for the correlation of outcomes within a cluster (site) using an exchangeable covariance structure and a bias correction factor to account for the small number of clusters [39]. The dependent variable will be clinical pathway adherence and the exposure variable will be the intervention status (core versus enhanced). The unit of analysis will be at the patient level to accommodate the weighting required by unequal cluster (site) sizes. Other independent variables will be added to the model if they are independently associated with adherence and/or their inclusion in the model changes the linear coefficient of the intervention effect by more than 20% in absolute value (i.e. effect modifiers).

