#### Secondary hypotheses

Adherence to the ADAPT CP and predictors of adherenceAdherence to each component of the ADAPT CP (yes/no) will be greater in the Enhanced implementation arm than in the Core implementation arm.Adherence to the ADAPT CP will increase from the 6- to 12-month follow-up.Staff-perceived individual and site readiness to change will be associated with adherence to the ADAPT CP.Staff use of the ADAPT resources will be associated with adherence to the ADAPT CP.Characteristics of the service (size, psychosocial staffing, existing psychosocial screening), will influence staff attitudes and adherence to the ADAPT CP.Greater awareness/use and perceived utility of implementation strategies will be associated with better adherence to the ADAPT CP.Acceptability of the ADAPT CP and resources7.The ADAPT CP will be acceptable to staff and patients.8.At least 60% of staff will be aware of, use, and rate as useful, the ADAPT resources (including the health professional training and the ADAPT Portal).ADAPT implementation strategies (Core and Enhanced)9.Both Core and Enhanced ADAPT implementation strategies will be feasible (delivered) and delivered with fidelity as planned.10.At least 60% of staff will be aware of, use, and rate as useful, both Core and Enhanced ADAPT implementation strategies.11.Acceptability, adoption, appropriateness, feasibility, fidelity, and penetration of implementation strategies will be greater in the Enhanced implementation arm than the Core implementation arm.12.Improvements in staff-reported acceptability of the ADAPT CP and perceived readiness to change will be greater at 6- and 12-month follow-ups in the Enhanced implementation arm compared to the Core implementation arm.Cost-effectiveness13.While more costly, the Enhanced implementation arm will achieve greater adherence than the Core implementation arm.Patient outcomes14.Anxiety and depression screening scores at rescreening will be significantly lower than at the initial screen.

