### Study design and setting

The study is a Cluster RCT being undertaken in the state of New South Wales (NSW), Australia. NSW health services are managed through 15 local health districts and three specialty networks. Twelve cancer services will be stratified by size of service - large (≥100 new pts./year) versus small (< 100 new pts./year)) to ensure equal patient volume in the two study arms. The sites will then be randomised at the cancer service level to a Core implementation strategy arm versus an Enhanced implementation strategy arm to facilitate uptake of the ADAPT CP.

After a 3-month period of site engagement, staff training and tailoring of the ADAPT CP and ADAPT Portal for each participating cancer service (site), that site will “go-live” and implement the ADAPT CP for 12 months, as part of routine care. ADAPT research staff will deliver the Enhanced or Core implementation strategies over that period, according to randomisation. The study uses a mixed methods design. Both quantitative and qualitative data eliciting staff attitudes to and experiences of the ADAPT CP and implementation strategies utilised, will be collected at T0 (baseline - after site engagement, at ADAPT go-live), T1 (6 months post go-live) and T2 (12 months post go-live).

Taking into account the governance, engagement and implementation phases, each site will participate in the study for a period of 18 months. Three sites will be activated every 3 months. Thus, all sites will have completed the study over a 30 month/2.5-year period.

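### The primary model's covariates are picked by a data-driven rule with an open candidate list; the rule fires on chance at site level and does not exclude post-allocation variables

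*Protocol article*

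**What the plan says.** The Primary analyses section of the protocol article specifies a patient-level GEE "using an exchangeable covariance structure and a bias correction factor to account for the small number of clusters". The terms named are these: "The dependent variable will be clinical pathway adherence and the exposure variable will be the intervention status (core versus enhanced"). It then gives a rule for enlarging the model. "Other independent variables will be added to the model if they are independently associated with adherence and/or" if "their inclusion in the model changes the linear coefficient of the intervention effect by more than 20% in absolute value (i.e. effect modifiers").

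The rule has two limbs joined by and/or: association with adherence, with no test level, and movement of the intervention coefficient. It sets no candidate list and no timing restriction.

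Three other places bear on it:

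- **Study design and setting:** "Twelve cancer services will be stratified by size of service". Size is not named as a term in the primary model.
- **Secondary hypotheses:** "Staff use of the ADAPT resources will be associated with adherence to the ADAPT CP". A further hypothesis there says the same of awareness, use and perceived utility of the implementation strategies.
- **Potential confounders:** lists staff and patient demographics and patient disease factors, but Primary analyses does not confine the rule to them.

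**The concern.** The confirmatory estimate should come from a model fixed in advance. Here the model depends partly on what each covariate does to the estimate under test. Four things follow.

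1. A percentage threshold on a coefficient near zero is easily crossed by chance. The final test is then carried out as though no selection had happened.
2. Staff use of resources and awareness of the strategies arise after allocation, and the protocol expects them to predict adherence. A variable that carries the effect of the Enhanced strategy will shift the coefficient for that reason. Adjusting for it removes part of the effect that the trial is meant to measure.
3. A shift in the coefficient signals confounding or chance imbalance. It says nothing about effect modification, so the bracketed gloss points the analyst to the wrong quantity.
4. There are only 12 sites. Each site-level covariate costs about one degree of freedom, and the stratifier is left to the same screen as any other variable.

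**Working it through.** **Inputs from the protocol article.** Power for primary endpoints gives "a conservative estimate of 464 screening events per site (total sample of 5568 screening events in 12 sites") and "a difference in adherence rates of 30% in the Core and 60% in the Enhanced arm using a two-tailed test with Type 1 error rate"; that error rate is set at 5%. It tolerates an ICC of 0.14 for 80% power and 0.10 for 90%. *Assumed:* six sites per arm, equal cluster sizes, and 20% read as a relative change.

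**Step 1: reproduce the plan's power.** Design effect = 1 + 463 × ICC, and effective n per arm = 2784 / design effect.

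- ICC 0.14: 65.82, so 42.3 per arm and power 80.3%.
- ICC 0.10: 47.3, so 58.9 per arm and power 91.5%.

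The stated figures hold, so the setting below is the plan's own.

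**Step 2: one noise site-level covariate, no true effect.** With equal clusters and an identity link, the GEE coefficient is the difference in site means. Adding covariate x changes it by g × d, where g is the pooled within-arm slope and d is the difference in arm means of x. If x is normal noise and there is no effect, d divided by the unadjusted coefficient is a scaled Cauchy variable, and g is a scaled t on 10 df. The scales cancel to leave

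P(|Cauchy| × |t₁₀| / √10 > 0.2) = E[1 − (2/π) arctan(0.2√10 / |t₁₀|)] = 0.494.

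ICC and cluster size drop out. Simulation agrees, at 49–50%.

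**Step 3: the same covariate with a true effect.** Site variance ≈ 0.225 × design effect / 464, where 0.225 is the mean of 0.3 × 0.7 and 0.6 × 0.4. At ICC 0.14 this is 0.0319, so the SE of the difference is √(0.0319 / 3) = 0.103 and effect/SE = 0.30 / 0.103 = 2.91. The larger this ratio, the harder it is for noise to move the coefficient by 20%.

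| True rates | Site-level noise passes (ICC 0.05–0.14) |
|---|---|
| 30% v 30% | 49–50% |
| 30% v 35% | 43–46% |
| 30% v 40% | 28–41% |
| 30% v 60% | 3–12% |

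A patient-level logistic GEE (300 runs per setting) gives 40–52% at the null and 3–17% at 30% v 60% for site-level noise. Patient-level noise passes in 6–9% and 0%. A few of these fits reached the iteration limit, so the patient-level rates are approximate.

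**Step 4: consequences for the test.** The number of candidates is an assumption.

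| Noise site-level candidates | At least one enters, null | Type I error | SD of estimate, null |
|---|---|---|---|
| 1 | about 50% | 5.0–6.3% | up about 5% |
| 2 | about 70% | about 6–7% | up about 10% |
| 5 | about 89% | about 7.5–8.5% | up about 30% |

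Without selection, type I error is about 5%. Adding the association limb, at an assumed p < 0.05, gives 8.1–8.6% with five. At 30% v 60% and ICC 0.14, five noise candidates lower simulated power by about 3–4 points; one candidate leaves it almost unchanged.

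**Step 5: a mediator.** *Assumed:* site-level mediator raised by 1 SD in the Enhanced arm, ICC 0.10, total effect 0.30, share s mediated. The adjusted effect is 0.30 × (1 − s).

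| s | Adjusted effect | Admitted by 20% limb | Mean reported effect |
|---|---|---|---|
| 30% | 0.21 | 62% | 0.22 |
| 50% | 0.15 | 87% | 0.15 |
| 80% | 0.06 | 97% | 0.06 |

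**The case against.** The best defence is that the practical harm is limited. The analysis is at patient level, and the patient variables under Potential confounders (age, gender, cancer type, stage and so on) are ones for which noise seldom passes. With one site-level candidate the type I error barely moves, and at the planned effect few noise covariates enter. This stands, and it limits the size of the point. It does not remove it: the secondary hypotheses name site-level characteristics (size, psychosocial staffing, existing screening), and the candidate set is open.

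Three stronger readings are tempting but not supported:

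- *That the rule takes type I error to a known level above 5%.* The level depends on how many site-level candidates are tried, which the article does not say.
- *That the sponsor plans to adjust for mediators.* No sentence says so. They appear as predictors in secondary hypotheses, and the Discussion treats mediators as material for future hypotheses. The accurate statement is that the primary rule does not exclude them.
- *That the stratifier is definitely left out.* Adjustment for stratification factors is often settled in the SAP, which is not shown. It can be said only that the article does not name size and that, as written, size would enter through the screen.

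Deferral to an SAP does not answer the main point. The article states the selection rule itself, so an SAP could repair it only by departing from that text.

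**Conclusion.** The concern holds as a should-fix. The primary analysis has a selection rule that uses the treatment estimate, has no closed list and has no timing restriction, and it misnames what a coefficient shift shows.

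For site-level noise, the 20% limb is close to a coin toss under no effect and a modest nuisance at the planned effect. Error inflation runs from negligible with one candidate to roughly 3 percentage points with five. The potentially larger harm is adjustment for a post-allocation variable, which could halve the reported effect if half of it were mediated. That is conditional on such a variable being tried and on an assumed mediated share.

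The figures rest on six sites per arm, equal cluster sizes, ICC 0.05–0.14 (0.10 for the mediator case), and a candidate count that the document does not give.

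**What to change.** Replace the selection sentence in Primary analyses with a fixed model:

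- Arm plus a short, named list of covariates measured before randomisation.
- Service size on that list, once its definition is settled. Study design and setting defines small as fewer than 100 new patients a year, while Inclusion criteria requires care of at least 100 patients a year; these passages must be reconciled first.
- An explicit bar on post-allocation variables in the primary model.
- Change-in-estimate models moved to sensitivity analysis, and mediator models to exploratory analysis.
- The effect-modifier gloss deleted, with modification examined through arm-by-covariate interactions.

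The change is to wording and should be made before outcome data by arm are seen. Each site-level term costs about one degree of freedom. For the size stratum at ICC 0.14 (effect/SE 2.91), power on a t reference goes from 74.6% on 10 df to 73.5% on 9 df, about one point. That is why the list should be short.
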